### Eight-month exercise intervention

Participants randomized into the intervention group will undergo a multicomponent exercise regimen. They will participate in supervised training three times a week for 8 months. Step aerobics and resistance training programs will alternate fortnightly. Each session will include a 10-min warm-up, a 30-min effective training session, and a 10-min cooldown. The intervention group will be divided into two to form smaller groups for the exercise sessions. Training sessions will be carried out by experienced and trained exercise instructors. Training sessions will be offered six times a week on various days and times to ensure that participants will be able to attend training three times a week. To ensure the intensity and suitability of the regimen, perceived exertion on the BORG 6–20 scale [78] will be assessed after every training session, along with knee pain on the visual analog scale, psychological readiness to train, and possible additional comments.

#### Step aerobics

Step aerobics training will be conducted at the Faculty of Sport and Health Sciences, University of Jyväskylä. The program includes accelerating and decelerating through forward, backward, and sideways movements with stops and turns to music. The choreographies included will use patterns such as basic steps, V-steps, knee lifts, side steps and jumps, and leaps and hops on and off the board. The tempo of the music for all sessions will be set to 120 beats per minute. The difficulty of the movements and the intensity of workouts will be gradually increased by increasing the height of the step boards and increasing the intensity of the movements. The program will be divided into four distinct 8-week phases. The program will start with a progressive orientation phase, which aims to teach participants the techniques of different steps used in the program. Phase 2 will increase the number of hops and the intensity of the steps and increase the board height to 15 cm at week 13. The third phase will increase the number of hops and jumps off the board performed at a height of 15 cm. The fourth phase will introduce a 5-cm increase in the height of the board while decreasing the number of hops. If a participant is unable to progress safely, the board height will be increased individually when it is appropriate and safe to do so. The characteristics of these phases are presented in Table 4.

**Table 4 Tab4:** Characteristics of step aerobics training in different phases

**Phase**	**Board height**	**Number of steps on the board***	**Number of hops**
Orientation (weeks 1–8)	10 cm	100 to 200	0 to 150
Phase 2 (weeks 9–16)	10 cm/15 cm	130 to 250	200
Phase 3 (weeks 17–24)	15 cm	200	180
Phase 4 (weeks 25–32)	20 cm	180 to 190	160

^*^The number of steps shown includes steps on the board only. Various steps that do not include a clear step on the board, i.e., touch steps from the board to the floor and stepping on the board and floor, are not included

#### Resistance training

Resistance training will be conducted at the University of Jyväskylä’s Sport and Health Sciences laboratory, and the program will emphasize training of the following muscle groups: quadriceps, hamstrings, hip abductors, adductors, and extensors. In addition to lower limb exercises, trunk and upper body exercises will be applied at intervals. Resistance training will be conducted mainly using air resistance equipment (HUR Oy, Kokkola, Finland). This equipment will save the participants’ training resistance, and the settings used, as well as increase the resistance automatically. When a participant performs 12 repetitions with a resistance, the system will increase the resistance for the next visit by 2 kg for the leg press and 0.5 kg for the other exercises. The resistance can also be changed manually if necessary. During the first training session, all adjustments for the exercises will be guided, and the starting loads will be determined individually for each participant. The participants will be instructed to aim for 12 repetitions in the exercises using an external load. Progression will follow a 2 + principle. For example, when a participant can perform 2 more repetitions in a set of 3 × 10, more load will be needed. Instructors will be monitoring the progressive increase in resistance during the program. Air resistance exercises will include hip adduction/abduction, trunk flexion/extension, inclined leg press, knee extension/flexion, and push up/pull down. Other exercises will be included depending on the number of participants in the practice. These exercises include hip flexion/extension in machine, bridge, plank, lateral band walk, calf raise, dead bug, squat press, biceps curl, and triceps pushdown. Resistance training will be conducted using cross training and two to three sets of each exercise will be performed. Kinetic exercises will include steady concentric and eccentric phases. A 30- to 60-s rest between the sets will be given. The exercises used in the program are described in more detail in Supplement 2.

### Reference group

The treatments provided to the reference group represent standard rehabilitative management for knee OA patients in Finland. The home exercises focus on functional exercises to maintain lower extremity flexibility and muscle function. The home exercises are described in Supplement 3. The home exercises will be instructed to be carried out three times a week, with each workout lasting 30 min. Members of the reference group will be instructed to keep a diary of their home exercise workouts to assess compliance. Otherwise, they will be asked to maintain their habitual physical activity during the intervention period.

### Twelve-month follow-up period

All participants will be advised to continue spontaneous physical activity for 12 months after the post-intervention measurements, whereas no other specific instructions will be given.

### Statistical analysis

Data will be analyzed with an intention-to-treat strategy, where all the enrolled participants will be included in the analysis in their randomized groups, regardless of protocol adherence. The mean change from baseline in the outcomes will be compared between the groups. One-way analysis of covariance (ANCOVA) with the 8-month endpoint and 12-month follow-up measurements as dependent variables will be used to assess the intervention effect between the groups. Cartilage and bone traits as outcome variables will be adjusted for baseline values, age, height, and body mass. In the association analyses, correlation coefficients will be calculated via the Pearson or Spearman methods with bootstrap-type confidence intervals. In addition, generalized linear models (GLM) with appropriate distributions and link functions will be provided for each outcome. Compliance with the intervention will be calculated using the following formula: [number of exercise sessions performed]: [expected number of exercise sessions] × 100. Statistical analyses will be performed using up-to-date versions of statistical software (Stata, StataCorp, College Station, TX and SPSS, IBM Corporation). Two-sided *p* values with alpha < 0.05 will be used for all tests, and 95% confidence intervals will be provided when the results are presented. A professional academic statistician blinded to the study groups will conduct the analyses.

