**Discussion:**

This RCT investigates the effectiveness of a multicomponent exercise regimen on the subchondral bone and cartilage of the knee joint and the potential interaction between these tissues. The information gained will improve our understanding of the effects of exercise on subchondral bone and the biochemical properties of articular cartilage and improve the prescription of multicomponent exercise regimens in the management of mild KOA.

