To our knowledge, there have been no publications investigating the effects of exercise on the interplay of subchondral bone and articular cartilage in people with knee OA. The aim of this study is to investigate the effects of a multicomponent exercise regimen on the subchondral bone and articular cartilage of the knee joint and the potential interactions between these tissues. With the information gained, we will be better able to prescribe multicomponent exercise regimens for the treatment of mild knee OA and better understand the effects of exercise on subchondral bone and the biochemical properties of cartilage.

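### The plan's only named method for bone-cartilage association is a bivariate correlation, with no statement that trial arm is controlled; pooled over arms, it can pick up a shared exercise effect as tissue coupling

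*Protocol article*

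**What the plan says.** The closing paragraph of the protocol article's Discussion gives as the trial's aim the effects of exercise on "subchondral bone and articular cartilage of the knee joint and the potential interactions between these tissues". The Discussion part of the Abstract likewise names "the potential interaction between these tissues". The Introduction and the Discussion both present this interplay as not yet studied in humans or in people with knee OA.

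Three sentences of the Statistical analysis section bear on the aim:

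- On covariates: "Cartilage and bone traits as outcome variables will be adjusted for baseline values, age, height, and body mass". This follows the ANCOVA sentence and concerns each tissue as a dependent variable in the comparison of groups.
- On association analyses: "correlation coefficients will be calculated via the Pearson or Spearman methods with bootstrap-type confidence intervals".
- On further models: "generalized linear models (GLM) with appropriate distributions and link functions will be provided for each outcome". No predictors are named, and nothing ties these models to the bone-cartilage question.

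The section does not say whether correlations are computed over both arms together or within each arm, whether they use changes or levels, or whether any covariate enters.

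**The concern.** Randomisation protects the comparison of arms. It does not protect the association between two outcomes measured in the same woman. If the programme moves bone and moves cartilage, women in the exercise arm sit apart from women in the reference arm on both axes. A coefficient over all participants then picks up that separation, even if the women whose bone changed most are no more likely than others to show a cartilage change.

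Such a correlation could be reported as crosstalk between tissues, the question the article presents as new, when it reflects only that one programme acted on each tissue separately. A bootstrap interval describes sampling error around the pooled coefficient. It does not change what that coefficient measures.

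**Working it through.** **Inputs from the protocol article.** Sample size section: 38 per group, 80% power, a 4 ms difference in T2, significance level 0.05, dropout about 15%, at least 90 recruited. Randomization section: equal group sizes. Statistical analysis section: "Two-sided *p* values with alpha < 0.05 will be used for all tests". No SD is given for T2. For subchondral bone, the Sample size section says that adequate prior data are lacking.

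**The plan's own figure.** 2 × 38 = 76, and 76 / 0.85 = 89.4, which rounds up to 90. This matches. The article gives no figure for the association analysis.

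**Standardised effect implied for T2.** The normal approximation is n per group = 2 × (1.960 + 0.842)² × (SD / 4)². With n = 38 this gives SD of about 6.22 ms, so d = 4 / 6.22 = 0.64. The t-test solution is d = 0.651, with SD 6.14 ms. I use 0.65. Applying it to bone is an assumption, so a range is shown.

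**Correlation induced by pooling.** Let the within-arm correlation be zero, the within-arm SDs be 1, allocation be 1:1, and the shifts be d1 and d2. Over both arms the covariance is 0.25 × d1 × d2 and the variances are 1 + 0.25 × d1² and 1 + 0.25 × d2². Hence

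r = 0.25 × d1 × d2 / √[(1 + 0.25 × d1²)(1 + 0.25 × d2²)].

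For d1 = d2 = 0.65, r = 0.1056 / 1.1056 = 0.096. For d1 = d2 = 1.0, r = 0.25 / 1.25 = 0.20.

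**Rejection rate by Fisher z, n = 76.** The test statistic is centred at atanh(r) × √73.

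- r = 0.096: centre 0.82, two-sided rejection about 13%.
- r = 0.20: centre 1.73, rejection about 41%.

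**Simulation check.** 20,000 trials per setting, true within-arm correlation zero, t-based tests in place of the bootstrap interval:

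| Shift in the two tissues (SD) | Induced r | Pearson rejection, n = 76 | Rejection after arm adjustment, n = 76 |
|---|---|---|---|
| 0.65 and 0 | 0.00 | 5.2% | 5.2% |
| 0.3 and 0.3 | 0.02 | 5.3% | 4.9% |
| 0.5 and 0.5 | 0.06 | 7.9% | 4.9% |
| 0.65 and 0.65 | 0.10 | 13.6% | 5.0% |
| 0.65 and -0.65 | -0.10 | 12.6% | 4.9% |
| 0.8 and 0.8 | 0.14 | 22.4% | 5.2% |
| 1.0 and 1.0 | 0.20 | 42.2% | 5.0% |

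Spearman behaves alike: 13.1% at 0.65 in both tissues. With 90 participants the Pearson rate there is 14.8%. Arm adjustment brings the mean correlation to 0.00 in every setting.

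**Sign.** The Magnetic resonance imaging section treats longer T2 as worse, and the Introduction expects exercise to enhance bone. A benefit in both tissues could therefore appear as opposite shifts. These induce a negative correlation, which offsets true positive coupling and inflates true negative coupling.

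**The case against.** The strongest reply is that the article never says the arms are pooled or the coefficients unadjusted. Correlations within each arm fit the text and are free of this artefact. The sentence on association analyses is not explicitly tied to bone and cartilage. The generalised linear models could carry arm and covariates. A condensed article may leave such detail to an analysis plan that is not at hand. Bone-cartilage interaction is also absent from the primary and secondary outcome tables.

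Much of this stands. A reader might infer that the plan commits to a pooled, unadjusted analysis, but the documents do not support that: the choice is left open. A reader might also infer that the method will show coupling where none exists. At 0.65 SD in both tissues, roughly 87% of null trials would still not reject, and with small effects or a shift in one tissue only there is practically no distortion. KL grade, age and body mass may also link the two tissues, but the documents give no figure for this, least of all for changes, so no size is claimed here.

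What does not fall away is that the article goes beyond silence. It names a tool for association, that tool is bivariate, and neither the covariate sentence nor the sentence on generalised linear models conditions the association on arm.

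**Conclusion.** The point holds in limited form. For an aim presented as novel, the plan names only a bivariate correlation and does not say that arm is controlled. If the arms are pooled and exercise moves both tissues, the coefficient is biased as a measure of coupling. The bias is about 0.10, with about 13% rejection, at 0.65 SD in both tissues, and 0.20 with about 41% at 1.0 SD. It is negligible at 0.3 SD or if only one tissue moves.

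These sizes assume zero within-arm correlation, normal data, equal arms and 76 completers. The bone effect is assumed throughout, and the T2 effect is back-solved rather than stated. A correlation at baseline would be unaffected, as would the between-group comparisons of the primary outcomes. The change is worth making because it removes the ambiguity cheaply.

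**What to change.** State that the bone-cartilage association is estimated on 8-month changes by a partial correlation adjusted for arm, or by regression of cartilage change on bone change with arm in the model, with bootstrap resampling stratified by arm. Label any raw pooled correlation as descriptive.

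Adding the covariates already used in the ANCOVA (both tissues' baseline values, age, height, body mass) and KL grade is a reasonable sensitivity analysis. An arm-by-bone-change term can be reported as exploratory. Neither is needed to remove the bias computed above.

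The cost is a few lines of analysis text. Adjusting for arm takes one degree of freedom (73 instead of 74 at 76 participants). The sensitivity analysis takes a few more and widens intervals slightly. No new data are needed. The Trial status section reports that the phase 1 post-intervention measurements are done, so the wording should be fixed before the association data are analysed.

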##### Health-related quality of life

The RAND-36-Item short-form health survey instrument [52] will be used to measure self-assessed quality of life. The 36 items of the RAND-36 measure eight different aspects of health, which are physical functioning, role limitations caused by physical health problems, role limitations caused by emotional problems, social functioning, emotional wellbeing, energy/fatigue, pain, and general health perceptions. All items are scored from 0 to 100, and scores within the same scale are averaged to create each scale. Higher scores represent a more favorable health state. The scores represent the percentage of the total possible score achieved. Cronbach’s *α* coefficients describing the internal consistency of the questions in a Finnish sample ranged from 0.80 to 0.94, with the highest being for physical functioning [53].

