#### Inertial measurement unit (IMU)

Five IMUs (NGIMU, X-IO Technologies, UK) will be used during the 40-m fast-paced walk test and stair climb test. In addition, the participants will be measured during a 2-min walk at their regular pace. During the 2-min walk, the participant will be asked to stop their movement before the turns to help identify changes in movement within the gathered data. The IMUs will be mounted on the participant’s both ankles, middle of both femurs, and lower back at the level of the umbilicus. The IMUs will be calibrated, and any gaps will be checked in the test data daily before beginning the measurements. The sensors will sample accelerations, gyrations, and magnetic field strengths 100 times per second with measurement ranges of ± 16 multiples of gravitational acceleration, ± 2000°/s, and ± 1300 µT, respectively, via 16-bit analog-to-digital conversion. Data will be recorded over a wireless Wi-Fi connection, and the sensors will be synchronized with each other using the manufacturer’s implementation. The data will be used to analyze the lower body’s segmental acceleration (m/s^2^) and to model flatland and stair walking. All secondary outcome measures are presented in Table 3.

**Table 3 Tab3:** Secondary outcomes

Measurement	Variables
Dual-energy X-ray absorptiometry	Femoral neck areal bone mineral density (aBMD, g/cm^2^), and bone mineral content (BMC, g), total body fat percentage, fat free mass index (kg/m^2^), and lean body mass (kg).
Advanced hip structure analysis	Femoral neck cortical thickness (mm), width (mm), cross-sectional area (CSA, cm^2^), cross-sectional moment of inertia (CSMI, cm^4^), section modulus (cm^3^), and strength index.
Questionnaires	General health questionnaire at baseline (supplement 1), International Physical Activity Questionnaire, RAND-36-Item short-form healthy survey, Knee injury and Osteoarthritis Outcome Score, short version of the Örebro Musculoskeletal Pain Screening Questionnaire, and rating of current work ability on a scale from 0 to 10.
Dynamometry	Maximal isometric knee extension and flexion muscle strength (Newton).
UKK 2-km walk test	Estimated maximal aerobic power, VO2 max (ml/kg/min).
Triaxial accelerometry	Light, moderate, and vigorous physical activity times; number of steps; standing, lying, and sitting times; number of breaks during sedentary time; total, low, medium, and high movement time in bed.

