Physical activity diary	Metabolic equivalent of task (MET)-hours and quantity of painkillers consumed.
Blood samples	Systemic inflammation markers and circulating metabolome, including resistin, leptin, adiponectin, lipids, and lipoproteins.
Physical function tests	30-s chair-stand test (repetitions), timed up and go test (s), 40-m fast-paced walk test (s), stair climb test (s), and single-leg stance test.
Inertial measurement unit	Lower body’s segmental acceleration (m/s^2^), modeling of walking, and stair climb.

Participant retention and loss to follow-up will be improved by reminding participants of upcoming measurements when the accelerometers are distributed to the reference group every 2 months, reminders within the instructed exercise sessions, making every reasonable effort to schedule measurements at compatible times, and if a participant cannot or refuses to participate in some of the measurements, offering them the opportunity to still participate in the other measurements.

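### The blanket p < 0.05 rule covers an open-ended inflammation and metabolome panel at two visits, with no false discovery control

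*Protocol article*

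**What the plan says.** The Statistical analysis section gives one significance rule: two-sided *p* "values with alpha < 0.05 will be used for all tests". The same sentence promises 95% confidence intervals. It names no multiplicity procedure and makes no exception for any group of outcomes.

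The intervention effect is assessed by ANCOVA, "with the 8-month endpoint and 12-month follow-up measurements as dependent variables will be used to assess the intervention effect between the groups". The section adds that "generalized linear models (GLM) with appropriate distributions and link functions will be provided for each outcome".

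The article states that "All secondary outcome measures are presented in Table 3". The blood entry in that table reads "Systemic inflammation markers and circulating metabolome, including resistin, leptin, adiponectin, lipids, and lipoproteins", and the Blood samples section describes the panel in the same open way. Neither place gives a list of analytes or a number. The Study design section has all outcomes measured at baseline, after the 8-month intervention and 12 months after training ends, so the panel is tested at two post-baseline visits.

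**The concern.** For a handful of prespecified secondary variables, an unadjusted 5% level is a familiar choice. A metabolome panel is different. It can hold many analytes, and few of them are likely to have a hypothesis of their own. Under a fixed p < 0.05 rule, the number of chance findings grows in proportion to the panel, and the article sets no limit on the panel.

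A statistician who followed the text would test each analyte at 0.05, at each visit, and report whatever crossed the line. The Introduction lists effects on molecular biomarkers of OA and inflammation among the trial's questions, so chance findings could be published as exercise effects on those biomarkers. The primary cartilage and bone comparisons are not affected by this point.

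**Working it through.** **Inputs from the article**
- Level: two-sided 0.05 for every test (Statistical analysis).
- Post-baseline visits: 2 (Study design; Statistical analysis).
- Named blood markers or classes: 5, namely resistin, leptin, adiponectin, lipids and lipoproteins (Table 3).
- Panel size and expected number of false positives: not stated, so there is no figure of the plan's own to reproduce.

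**Assumptions**
- Panel of m = 100 to 250 analytes, used only to show scale.
- All analytes null, unless a fraction is given.

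**Blood panel under the written rule**

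Expected false positives per visit = (number of truly null analytes) × 0.05. Correlation between analytes does not change this expectation.

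| Truly null analytes | Per visit | Over two visits |
|---|---|---|
| 5 (named items only) | 5 × 0.05 = 0.25 | 0.5 |
| 100 (assumed) | 100 × 0.05 = 5 | 10 |
| 250 (assumed) | 250 × 0.05 = 12.5 | 25 |

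If half the analytes in the assumed panel respond to exercise, the per-visit figures halve to 2.5 and 6.25. Lipids and lipoproteins are classes that can each hold several analytes, so 5 is a minimum count.

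**Blood panel under Benjamini-Hochberg at 5%**

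The ordered p values p(1) ≤ … ≤ p(m) are compared with 0.05 × i/m. The first step is 0.05/100 = 0.0005 for 100 analytes and 0.05/250 = 0.0002 for 250. If every analyte is null, the false discovery rate equals the chance of any rejection, so that chance is held to 5% per visit under independence or positive dependence.

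**The remaining secondary outcomes**

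The Table 3 count depends on the counting rule. Three groups are fixed: DXA 5 (including "total body fat percentage, fat free mass index (kg/m^2^), and lean body mass (kg"), hip structure 6 (ending with "section modulus (cm^3^), and strength index") and accelerometry 12. The questionnaires move the total most: "The 36 items of the RAND-36 measure eight different aspects of health", and the KOOS has five dimensions.

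- Low count (one score per questionnaire): 5 DXA + 6 hip structure + 5 questionnaire + 2 strength + 1 VO2 max + 12 accelerometry + 1 diary + 3 blood + 5 function + 1 IMU = 41.
- High count (separate questionnaire scales, each leg): 5 + 6 + 20 + 4 + 1 + 12 + 2 + 6 + 5 + 3 = 64.

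The high count includes diary MET-hours. The Physical activity diary section has that diary kept by the reference group only, so it is not a between-group test. The low count already leaves it out. Removing the blood items from both counts, and MET-hours from the high one, leaves 41 − 3 = 38 to 64 − 6 − 1 = 57 variables. At 0.05 each this is 1.9 to 2.85 expected false positives per visit if all nulls are true. With the blood items left in, 41 to 64 variables give 2.05 to 3.2. Either way the figure is about two to three.

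**The case against.** The strongest reply is that a journal article condenses its plan. Handling of an omics panel is the kind of detail a statistical analysis plan supplies, and a stated nominal level does not say that no adjustment will be made. This has force: silence on multiplicity would not be a finding. But the article is not silent. It fixes one threshold for all tests, gives no exception and refers to no later rule. If an analysis plan already controls the false discovery rate in this panel, the remaining step is to align the two documents.

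It can also be said that the panel size of 100 to 250 is assumed. That stands. The documents support only the rate of 0.05 per null analyte per visit and the minimum of five named items.

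A reader might infer something stronger: that the rule puts every secondary outcome on a level with the primary ones and makes false positives near certain across some 59 secondary variables. The documents do not support this.
- Outcomes are ranked. Table 2 is headed primary and Table 3 secondary, and the Introduction makes 8 months the primary timepoint. A shared threshold is not shared evidential standing.
- A 95% chance of at least one false positive (1 − 0.95^59 = 0.95) needs 59 independent true nulls. In a simulation of 59 equally correlated null tests, the chance fell to 0.845, 0.657 and 0.425 at correlations of 0.3, 0.5 and 0.7. Hip geometry indices, KOOS dimensions and in-bed movement times are plainly related to each other.
- Eight months of strength and aerobic training may have real effects on some variables, so not all nulls need be true.
- The GLMs do not double the testing. ANCOVA is the model given for the intervention effect, the GLMs come in addition, and both use the same data.
- Leaving ordinary secondary outcomes unadjusted is common practice, and confidence intervals are already planned.

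**Conclusion.** The point holds for the inflammation and metabolome panel. Applied as written, the rule yields 0.05 expected false positives per truly null analyte per visit: 0.25 for the five named items, and 5 to 12.5 if the panel has 100 to 250 analytes and all are null. The rate follows from the text. The larger figures rest on an assumed panel size and shrink in proportion to the share of analytes with real effects.

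It does not extend to a demand for adjustment across all secondary outcomes. Their two to three expected false positives per visit are an upper figure that assumes no real effects, and they can be handled by reading those results as supportive. The point is moderate: it bears on the biomarker claims and leaves the main conclusion untouched.

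**What to change.** In the Statistical analysis section, or in the analysis plan with the article's rule aligned to it:

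1. Exempt the inflammation and metabolome panel from the blanket 0.05 rule. Apply Benjamini-Hochberg control of the false discovery rate at 5% within the panel, separately at 8 months and at the 12-month follow-up, using the ANCOVA p values.
2. List the analytes in the panel before the group comparisons are run, so that the family is fixed.
3. Leave the other secondary outcomes unadjusted and state that they are supportive, read from the estimates and 95% confidence intervals already planned.

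The cost is a few sentences and a routine computation, with no change to sample size, visits or trial conduct. The downside is that fewer biomarkers will be nominally significant, and a weak real effect on a single analyte will be harder to declare.
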